A total of 143 local ADRs were reported during the study period by 21 subjects (95.5%). The number of local ADRs reported increased with increasing dose of COR-1. Erythema and induration were the most frequently reported injection site reactions, occurring in at least one subject in each treatment group at some point during the vaccination phase. Erythema was reported more frequently in the 100 mcg, 300 mcg and 1 mg COR-1 treatment groups. Induration was reported more frequently in the 1 mg COR-1 treatment group. All injection site reactions were classified as mild in intensity.

A total of 14 systemic ADRs were reported during the study period by four subjects (18.2%). The most frequently reported were headache, fatigue, chills, malaise, pain and pyrexia. There were no trends in the frequency of systemic ADRs by treatment group. All the systemic ADRs reported were classified as mild in severity.

Review of haematology and biochemistry results revealed no trends or notable changes over time following vaccination with COR-1 at any dose level. There were no trends or notable findings in vital signs following each vaccination with COR-1 at any dose level.

A review of the safety data suggests that 3 ID vaccinations of the COR-1 vaccine at three weekly intervals were safe and well tolerated.

No anti-HSV gD2 antibodies were detected in any subject by ELISA, indicating that no subjects had seroconverted to COR-1 during the study based on the utilised method.

IFN- $\gamma$  production by T cells specific for gD2 antigen was induced in 19 of the 20 subjects who completed the study as planned and was considered a cell-mediated response to the COR-1 vaccine. The response rates were similar in all treatment groups with 100.0% of subjects responding to the COR-1 vaccine in the 10 mcg, 30 mcg, 300 mcg and 1 mg groups and 75.0% responding in the 100 mcg group.

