### 4.2 Endpoints

#### Primary endpoints:

The primary endpoints of this study are:

- Incidence and severity of adverse events in each treatment group, including vaccine related adverse events:
  - Incidence and severity of local reactions (soreness, redness, induration, ecchymosis, oedema, itching and paraesthesia) at the site of vaccination;
  - Incidence and severity of systemic reactions (fatigue, myalgia, malaise, fever, rigors, arthralgia, nausea, diarrhoea, light headedness, dizziness, hypersensitivity and headache).

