### 8.2 Adverse Events

An adverse event or adverse experience (AE) is any untoward medical occurrence in a subject or clinical investigation subject administered an investigational product (whether it is the experimental product or the control) and which does not necessarily have a causal relationship with the investigational product. An AE can therefore be any unfavourable and unintended sign, symptom, or disease temporally associated with the use of a medicinal product, whether or not considered related to the medicinal product. Pre-existing events, which increase in frequency or severity or change in nature during or as a consequence of use of a drug in human clinical trials, will also be considered as adverse experiences. AEs may also include pre- or post-treatment complications that occur as a result of protocol-mandated procedures (e.g. invasive procedures such as biopsies).

Any AE (i.e. a new event or an exacerbation of a pre-existing condition) with an onset date after obtaining written informed consent up to the last day on study (including the follow-up, off study medication period of the study), should be recorded as an AE on the appropriate CRF page(s).

An AE **does not** include:

- Medical or surgical procedures (e.g. surgery, endoscopy, tooth extraction, transfusion); the condition that leads to the procedure is an adverse event;
- Pre-existing diseases or conditions present or detected prior to start of study product administration, that do not worsen;
- Situations where an untoward medical occurrence has not occurred (e.g. hospitalisation for elective surgery, social and/or convenience admissions);
- Overdose of either study product or concomitant medication without any signs or symptoms unless the subject is hospitalised for observation.

The subject will be instructed on the completion of the Diary Booklets that will serve as supporting documentation for solicited signs or symptoms after each vaccination including local injection site reactions and systemic symptoms and also genital HSV-2 symptoms (during swabbing assessments). Entries in the diary booklets shall be evaluated and graded for severity and causality by the Investigator (see Section 8 and Appendix 2). Clinically significant signs and symptoms reported in the diary card will be entered in the CRF.

Injection site reactions may include:

- Pain/tenderness;
- Erythema;
- Swelling/Induration; or
- Other.

Systemic symptoms may include:

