### 8.3.2 Clarification of Serious Adverse Events

Death is an outcome of an AE, and not an AE in itself. In reports of death due to “Disease Progression”, where no other information is provided, the death will be assumed to have resulted from progression of the disease being treated with the study product(s).

All deaths, regardless of cause, must be reported to Sponsor for subjects on study and for deaths occurring within 30 days of last study product dose or within 30 days of last study evaluation, whichever is longer.

“Occurring at any dose” does not imply that the subject is receiving study product at the time of the event. Dosing may have been given as treatment cycles or interrupted temporarily prior to the onset of the SAE, but may have contributed to the event.

“Life-threatening” means that the subject was at immediate risk of death from the event as it occurred. This does not include an event that might have led to death, if it had occurred with greater severity.

Complications that occur during hospitalisations are AEs. If a complication prolongs hospitalisation, it is a SAE.

“In-patient hospitalisation” means the subject has been formally admitted to a hospital for medical reasons, for any length of time. This may or may not be overnight. It does not include presentation and care within an emergency department.

The Investigator should attempt to establish a diagnosis of the event based on signs, symptoms and/or other clinical information. In such cases, the diagnosis should be documented as the AE and/or SAE and not the individual signs/symptoms.

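### The diagnosis-over-symptoms rule in Section 8.3.2 has no exception for the systemic reactions named in the primary endpoint, so that component can be undercounted and graded on a different scale

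*Protocol*

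**What the plan says.** - **Endpoint (Section 4.2).** The umbrella is "Incidence and severity of adverse events in each treatment group, including vaccine related adverse events". Beneath it sit a list of local reactions, "Incidence and severity of local reactions (soreness, redness, induration, ecchymosis, oedema, itching and paraesthesia) at the site of vaccination", and a systemic list of 12 terms, "Incidence and severity of systemic reactions (fatigue, myalgia, malaise, fever, rigors, arthralgia, nausea, diarrhoea, light headedness, dizziness, hypersensitivity and headache").
- **Diagnosis rule (Section 8.3.2, the SAE clarifications).** "The Investigator should attempt to establish a diagnosis of the event based on signs, symptoms and/or other clinical information". Then: "In such cases, the diagnosis should be documented as the AE and/or SAE and not the individual signs/symptoms".
- **Diary rule (Section 8.2).** The diary booklets serve as "supporting documentation for solicited signs or symptoms after each vaccination including local injection site reactions and systemic symptoms". The Investigator grades the entries for severity and causality, and "Clinically significant signs and symptoms reported in the diary card will be entered in the CRF".
- **What the diaries contain (Section 6.4.10).** The Injection Site Reaction Diary runs for 7 days after each vaccination. It lists pain/tenderness, swelling/induration, erythema and other findings. The only other relevant statement is a general one that the booklets have room for adverse events.
- **Local reactions (Section 6.4.2).** Injection sites are inspected and reactions graded at every visit after Visit 5, and any reaction is to be captured as an AE.
- **Analysis (Section 11.1.4).** The analysis focuses on subject incidence of treatment-emergent AEs, tabulated by preferred term and system organ class.

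**The concern.** One component of the primary safety endpoint counts named symptoms. One recording rule tells the Investigator not to write symptoms down once a diagnosis explains them. Another rule has symptoms entered. Nothing says which prevails, so two investigators could record the same post-dose episode differently.

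A later SAP cannot repair this, because a symptom that never reached the CRF cannot be recovered from a diagnosis line. At stake are the completeness of the named systemic list, the grade attached to each reaction, and comparability with Phase I, which Section 3.2.4 reports symptom by symptom.

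**Working it through.** The protocol states no figure on this point, so the check is mainly a comparison of texts, followed by a short illustration.

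**1. Reach of the rule.** The sentence stands under an SAE heading, but its wording covers AEs as well as SAEs. It operates only where a diagnosis is reached. No sentence in Sections 4.2, 6.4.10, 8.2, 8.2.1 or 8.3.2 exempts solicited reactions.

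**2. Is there an itemised back-up record?**
- Local: yes. The diary has separate items (6.4.10) and any reaction becomes an AE (6.4.2).
- Systemic: none is described. Section 8.2 says the diaries document systemic symptoms, but the diary described in 6.4.10 lists local items only. What remains is the general AE space in the booklets and the Observation Form (6.3.1.2), neither with named symptom fields. The AE page may be the only structured record, and 8.3.2 governs that page.

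**3. Effect on grade.** Of the 12 systemic terms, six have their own row in Appendix 2: fever, nausea, diarrhoea, headache, fatigue and myalgia. A diagnosis would be graded on the Systemic Illness row or on Table 8. Take an invented subject with a temperature of 39.2 °C, headache and myalgia, some interference with activity and no medical intervention:

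| | Recorded by symptom | Recorded as one diagnosis |
|---|---|---|
| Fever | Grade 3 (39.0–40 °C) | not recorded |
| Headache | Grade 2 | not recorded |
| Myalgia | Grade 2 | not recorded |
| Diagnosis | – | Grade 2 (Systemic Illness) |
| Named systemic reactions | 3 | 0 |
| Subject has any AE | yes | yes |

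The subject stays in any-AE incidence but leaves the named list, and the worst recorded grade falls from 3 to 2.

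**4. Illustration from Phase I (Section 3.2.4).** Inputs: 22 subjects dosed, and 14 systemic adverse drug reactions in 4 subjects.
- Stated incidence reproduced: 4/22 = 18.2%.
- Reactions per affected subject: 14/4 = 3.5, so several per subject did occur.
- If every reaction were replaced by an unlisted diagnosis: named systemic incidence 0/22 = 0%; any-AE incidence from these subjects still 4/22 = 18.2%.
- If none were replaced: named systemic incidence 4/22 = 18.2%.

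The upper figure assumes that each of the four had at least one reaction on the Section 4.2 list. The commonest Phase I terms include chills and pain, which are not on it under those names.

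**5. Weight of one subject here.** With 15 per COR-1 sub-group and 5 per placebo sub-group (Section 6.5), one subject recorded differently moves a named incidence by 1/15 = 6.7 or 1/5 = 20 percentage points.

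**The case against.** The strongest reply is that the specific rules already govern. Section 8.2 gives solicited symptoms their own path from diary to grading to CRF, Section 8.2.1 sends systemic signs and symptoms to Appendix 2, and Appendix 2 grades several of them singly. The diagnosis sentence closes a section about deaths, hospitalisation and other serious events, and it applies only when a diagnosis is made. A sensible investigator could read the rules together and lose nothing. That is why the loss may be zero. It does not remove the point: the sentence names AEs expressly, and nothing gives the diary path precedence.

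Four stronger readings are tempting and not supported:
- **That clustered reactions vanish from the primary safety result.** They do not. A diagnosis is still an AE with a severity and a causality, and it counts under the umbrella endpoint.
- **That local reactions are lost too.** Sections 6.4.2 and 6.4.10 collect them item by item.
- **That 14% to 71% of reactions would be lost.** A reader could get this by shrinking 14 events to 12 subject-doses (4 × 3) or to 4 subjects. Those are event counts, whereas Section 11.1.4 focuses on subject incidence. Nor is 14% a floor: 14 reactions over 12 subject-doses leave at least 10 with a single symptom and no cluster to merge, and with no diagnosis made the loss is 0%. The documents give no timing for the Phase I reactions.
- **That the bias is greater in the COR-1 arms.** This is plausible but not shown. The same rule applies to all arms and the assessors are blinded.

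It is also fair that the choice of terms feeding a table is SAP detail. What gets recorded at all is not.

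**Conclusion.** The concern holds for the named systemic reactions only. Section 8.3.2, applied as written to post-vaccination symptoms, conflicts with Section 8.2 and can leave a stated component of the primary endpoint undercounted. For the six symptoms with their own Appendix 2 row, it can also move grading to a different scale. Any-AE incidence and the local reactions stand.

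The size is not estimable from the protocol. The Phase I range of 0/22 to 4/22 marks what the two rules permit and predicts nothing. It rests on how often investigators would make a diagnosis, which is unknown, and on all four affected Phase I subjects having had a reaction on the Section 4.2 list. The correction is worth making because unrecorded symptoms cannot be restored at analysis and the change is small.

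**What to change.** 1. In Sections 8.3.2 and 8.2.1, state that each systemic reaction named in Section 4.2 that occurs after a vaccination is recorded and graded under its own term, and that any unifying diagnosis is recorded in addition and linked to those terms.
2. State that the incidence and worst grade of the named reactions are taken from the individual terms.
3. Reconcile Section 8.2 with Section 6.4.10: either give the post-vaccination diary fields for the named systemic symptoms, or say where else they are solicited.
4. State the collection period for systemic symptoms. The 7 days in Section 6.4.10 are set for injection-site reactions only.

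The cost is a few sentences in the protocol, matching lines in the CRF guidance, a diary revision if that route is chosen under item 3, and a few more AE lines per subject. The linkage is needed so that an episode recorded both as symptoms and as a diagnosis is not counted twice in total event counts.

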### **8.3.3 Serious adverse event reporting requirements**

#### **8.3.3.1 All SAEs**

Admedus Vaccines Pty Ltd has requirements for expedited reporting of SAE’s meeting specific requirements to worldwide regulatory authorities; therefore, all appropriate parties must be notified immediately regarding the occurrence of any SAE that occurs after the first dose of study product has been administered. The procedures for reporting all SAEs, regardless of causal relationship, are as follows:

- Complete the “Serious Adverse Event Report” Form:
  - Email the SAE report within 24 hours of the Investigator’s knowledge of the event (Please refer to the Study Reference Manual for the designated email address);
  - For fatal or life-threatening events, also fax copies of hospital case reports, autopsy reports, and other documents when requested and applicable.

Admedus Vaccines Pty Ltd may request additional information from the Investigator to ensure the timely completion of accurate safety reports.

The Investigator must take all therapeutic measures necessary for resolution of the SAE. Any medications necessary for treatment of the SAE must be recorded onto the concurrent medication section of the subject’s CRF.

#### **8.3.3.2 Investigator reporting requirements for SAEs**

An SAE may qualify for reporting to regulatory authorities if the SAE is considered to have a possible causal relationship to the study product, and is unexpected (Suspected Unexpected Serious Adverse Reaction [SUSAR]) based upon the current Investigator’s Brochure. In this case for multi-centre studies, all Investigators will receive a formal notification describing the SAE.

Where this is required by local regulatory authorities, and in accordance with the local institutional policy, the Investigator should notify (in writing) the Human Research Ethics Committee (HREC) which approved the study of the SAEs, according to the HREC requirements as soon as is practical.

### **8.4 Follow up of Serious and Non-serious Adverse Events**

Follow-up of serious and non-serious AEs will continue through the last day on study (including the follow-up, off study medication period of the study), until the Investigator and/or Admedus Vaccines Pty Ltd determine that the subject’s condition is stable, or up to 30 days after the last dose of Study Product, whichever is longer. Admedus Vaccines Pty Ltd may request that certain AEs be followed until resolution.

## 8.5 Clinical Laboratory Abnormalities and Other Abnormal Assessments as AEs or SAEs

All laboratory values must be reviewed by the Investigator. Given that all laboratory data are collected and statistically analysed according to their respective toxicity gradings, laboratory abnormalities that occur without related clinical symptoms and signs should generally not be recorded as an AE unless they are considered clinically significant by the Investigator. Where possible, the overall diagnosis rather than the laboratory abnormality should be recorded on the CRF. This will avoid duplication of laboratory abnormalities in both the CRF and laboratory reports. Abnormal laboratory results that are of clinical significance should be reviewed by the Medical Monitor.

Any laboratory test result that meets the criteria for a SAE (refer to Section 9.3) should be recorded as an AE, the AE page of the CRF completed and a SAE form also completed in order for the Sponsor to collect additional information about that abnormality, including information regarding relationship to study product or other causes, any action taken and resolution.

## 8.6 Guidance for dose modification or discontinuation of treatment

To date, no specific toxicities have been identified that result from COR-1 treatment. Any toxicities and/or abnormal laboratory findings should be investigated for aetiology and graded according to Section 9.2 and Appendix 2.

The following toxicity management will be followed:

- Grade 1 or 2: Patients may continue study vaccination/placebo (except if they have an elevated temperature of  $>38$  degrees Celsius or inter-current systemic illness). Dosing may be delayed for up to one week. Any dosing delays of  $>$  one week may require that the subject is withdrawn after discussion with the Medical Monitor. Safety assessments will occur immediately prior to each dosing of investigational vaccine/placebo.
- Grade 3: Patients with any Grade 3 toxicity considered to be at least possibly related to treatment (i.e. treatment related events) should be evaluated carefully by the Investigator prior to continuing study vaccination/placebo treatment. Investigators may discuss individual cases with the Medical Monitor.
- Grade 4: Patients developing any Grade 4 toxicity should have treatment interrupted. The Investigator should contact the Medical Monitor to discuss the subject's withdrawal.

Subjects will be withdrawn from treatment permanently should any of the following occur:

- Treatment related Grade 3 or 4 toxicity
- The need to take medication which could interfere with study measurements
- Subject unwilling to proceed and/or consent is withdrawn.

Where possible subjects who are withdrawn from treatment will remain on the study and attend the scheduled study visits, provided the Investigator deems it appropriate and the Sponsor approves.

Dosing will be stopped if suspected adverse drug reactions, changes to vital signs or clinical laboratory results are observed and these changes pose a significant health risk.

A corresponding adverse event will be captured within the CRF.

For any subject experiencing any event (irrespective of severity) which, in the opinion of the Investigator, contraindicates further dosing in that subject and the event is considered to be at least possibly related to treatment (or where causality to study treatment cannot be ruled out – see Section 9.2.1), continued dosing of the subject should be interrupted. In all cases, the final treatment decisions, made in response to toxicity, are the responsibility of the Investigator. A careful evaluation of the potential risk/benefit will dictate the optimal therapeutic course. Should treatment be interrupted, re-

initiation will follow review of the available safety data and in agreement with the Sponsor. There will be no dose reduction or modification.

If the Investigator deems that management of the patient's medical condition requires knowledge of the study treatment regimen, then the Medical Monitor must be contacted for consultation and the procedures described in Section 7.3 followed. If a patient dies from an event that is considered to be at least possibly related to treatment, continued dosing of all study participants should be interrupted.

Clinically significant suspected adverse drug reactions, and serious adverse events considered to be related to study procedures will be followed until resolved or considered stable. All subjects who experience a study drug related AE should be followed until resolution of the AE, even if the subject has discontinued study drug.

If an unscheduled interruption of study drug occurs, the study site should notify the Sponsor at the earliest possible time. In the event that a subject requires an unscheduled interruption of study drug under conditions other than those associated with toxicity, the case will be reviewed by the Sponsor to determine whether such a subject will be allowed to resume study drug.

Subjects withdrawn from study drug will be treated as deemed appropriate by the Investigator. Follow-up procedures should be performed and the appropriate CRFs should be completed.

The study may be terminated at any point in time at the discretion of the Sponsor.

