| Contraindications to further dosing: | 
Subjects will be withdrawn from treatment permanently should any of the following occur:
 
 
• Treatment related Grade 3 or 4 toxicity
 
• The need to take medication which could interfere with study
 
                                                                                                                                                                                                                                                                                                                                                                                                                                                                                                                                                                                                                                                                                                                                                                                                                                                                                                                                                                                                                                                                                                                                                                                                                                                                                                                                                                                                                                                                                                                                                                                                                                                                                                                                                                                                                                                                                                                                                                                                                                                                                                |

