## **6.6 Blinding**

Since the investigational vaccine is more viscous as compared to the placebo, it will not be possible to blind the study site member who administers the investigational vaccine. The pharmacy team members will also be unblinded. At the commencement of the study, the blinded investigational vaccine administrators will be identified and trained. There will be at least 2 investigational vaccine administrators at each site who have received training in the delivery of intradermal injections. The investigational vaccine administrators will not be permitted to be involved in patient assessments or management throughout the trial. Additionally they will not discuss what they believe the subject is receiving with either the subject or other staff members.

All other site staff and the subject will be blinded to the study treatment, COR-1 or placebo. Admedus Vaccines Pty Ltd and its representatives will also be blinded to the study treatment throughout the course of the study. The investigational vaccine administrator's will make every attempt to ensure that both the subject and the blinded team members do not observe the intradermal injection as this may threaten the integrity of the blind. The subject may place their forearm through a screen which blocks their view or may be asked to turn away during the injection. Similarly site staff will be instructed to not observe the administration of the investigational vaccine/placebo. This will be highlighted during the site initiation visit and throughout the study.

An unblinded monitor will perform drug accountability according to the Monitoring Plan.

The dose and injection regimen will not be blinded.

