### **10.3 Withdrawal of subjects from Study Product**

Section 8.6 provides guidance for dose modification or discontinuation of Study Product in the event of AEs or abnormal laboratory values.

If a subject permanently discontinues dosing with Study Product, for example as a result of an AE, every attempt should be made to keep the subject in the study and continue to perform the required study related follow-up and procedures.

The ideal is to continue to follow the subject for the full study period or until resolution of the adverse event. If it is not possible for the subject to remain in the study for the full study period, every attempt should be made to keep the subject in the study up to the Exit Evaluation at Day/Week . If the subject remains in the study but off study treatment, all study procedures should continue as per protocol.

If the subject will not remain in the study for all study related procedures, the Exit Evaluation should be performed wherever possible.

All subjects who discontinue study medication dosing should be followed for at least 30 days after the last dose of Study Product in order to monitor subjects for possible post-treatment events which may occur after Study Product has been discontinued.

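### Section 8.6 contradicts itself and the synopsis on treatment-related Grade 3 toxicity: one line allows further dosing, the other two require permanent withdrawal from treatment

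*Protocol*

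**What the plan says.** Protocol Section 8.6 sets out toxicity management by grade.

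- **Grade 3, at least possibly related.** The line states in brackets that these are the treatment-related events. The subject "should be evaluated carefully by the Investigator prior to continuing study vaccination/placebo treatment", and the Investigator may discuss the case with the Medical Monitor.
- **Grade 4, any cause.** "Patients developing any Grade 4 toxicity should have treatment interrupted", and the Investigator is to contact the Medical Monitor to discuss withdrawal.

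Directly below comes a separate list: "Subjects will be withdrawn from treatment permanently should any of the following occur". Its first item is related toxicity of Grade 3 or 4. The synopsis, under contraindications to further dosing, has the same lead-in and the same trigger: "Treatment related Grade 3 or 4 toxicity".

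Later in Section 8.6, two more sentences bear on the decision. "In all cases, the final treatment decisions, made in response to toxicity, are the responsibility of the Investigator". And where treatment has been interrupted, re-"initiation will follow review of the available safety data and in agreement with the Sponsor".

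Section 10.3 adds no rule of its own: "Section 8.6 provides guidance for dose modification or discontinuation of Study Product in the event of AEs or abnormal laboratory values".

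**The concern.** This is the stopping rule for the individual subject in a trial whose primary objective is safety and tolerability. For a related Grade 3 event, an Investigator can cite one line of Section 8.6 for giving the next vaccination and another for never giving it. The stake is subject protection: further vaccination after an event that the synopsis calls a contraindication.

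Grade 3 is not confined to dramatic events. Section 8.6 grades toxicities and abnormal laboratory findings by Appendix 2, where Grade 3 includes erythema above 10 cm, systolic pressure above 155 mm Hg, potassium of 5.5 to 5.6 mEq/L and a haemoglobin fall of 2.1 to 5.0 g/dL from baseline.

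**Working it through.** The protocol states no figure on this point, so the check is mainly a comparison of texts.

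**Step 1. Set the rules side by side.**

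| Event | Grade-specific line, 8.6 | List in 8.6, and synopsis | Can both be followed? |
|---|---|---|---|
| Related Grade 3 | Evaluate, then dosing may continue | Permanent withdrawal from treatment | No |
| Related Grade 4 | Interrupt, discuss withdrawal | Permanent withdrawal from treatment | Yes, in sequence: interrupt, assess causality, withdraw if related |
| Unrelated Grade 4 | Interrupt, discuss withdrawal | Not covered | Yes |

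**Step 2. Test whether scope reconciles the Grade 3 row.** The Grade 3 line covers events at least possibly related and equates them with treatment-related events. The list and synopsis cover treatment-related events. The scope is the same and the consequences exclude each other.

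**Step 3. Look for a line that says which governs.** The later discretion and re-initiation sentences in Section 8.6 do not mention the list. Section 10.3 refers back to 8.6. Section 9 gives the Safety Review Committee review of safety data and dosing decisions, but does not settle the rule for one subject.

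**Step 4. Size for one affected subject.** There are 4 vaccinations (Baseline, Weeks 4, 8 and 24; Section 6.8.3). After an event at dose k, 4 − k remain:
- k = 1: 3 of 4 (75%)
- k = 2: 2 of 4 (50%)
- k = 3: 1 of 4 (25%)

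The rule covers vaccine and placebo alike, and relatedness is judged blind (Section 6.6: "All other site staff and the subject will be blinded to the study treatment, COR-1 or placebo"), so all 40 planned subjects are in scope: 40 × 4 = 160 vaccinations. One affected subject puts at most 3/160 = 1.9% of these in doubt. Within one COR-1 group of 15 subjects (15 × 4 = 60 vaccinations), the figure is at most 3/60 = 5%.

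**Step 5. How often the rule might be needed.** The protocol gives no event rate. With an assumed true per-subject rate p, expected cases are 40p and the chance of at least one is 1 − (1 − p)^40:

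| Assumed p | Expected cases | Chance of at least one |
|---|---|---|
| 0% | 0 | 0% |
| 1% | 0.4 | 33% |
| 2% | 0.8 | 55% |
| 5% | 2.0 | 87% |

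Section 3.2.4 points to the low end. Among the 22 Phase I subjects, all injection-site and systemic reactions were mild, and the three severe events belonged to a clavicle fracture judged unrelated. Individual laboratory and vital-sign grades are not reported there, so no rate can be taken from that study.

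**The case against.** The strongest reply is that the strict rule plainly prevails. It says that subjects will be withdrawn, it names the exact trigger, and the synopsis repeats it, while the grade-specific lines use softer verbs. There are also safeguards. Safety assessments precede every injection. Dosing stops if changes pose a significant health risk. The Safety Review Committee meets regularly, meets at once if a concern arises, and reviews all available safety data before the first booster. The study is planned as single-centre for now (Section 4.5), which limits differences between sites.

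Much of this stands and lowers the severity. It makes re-dosing less likely, but it does not remove the contradiction. The Grade 3 line sits under text saying that the stated management will be followed, and it plainly contemplates further dosing. It requires no interruption, so the Sponsor-agreement step for restarting need not arise, and Medical Monitor discussion is optional.

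Two stronger readings are tempting, and the protocol does not support them.

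- **That Grade 4 is contradicted in the same way.** The Grade 4 line covers any cause and nowhere permits dosing after a related event. Interruption followed by mandatory withdrawal of related cases satisfies both texts. The defect is that the line speaks only of discussing withdrawal.
- **That the discretion and re-initiation sentences license overriding the list.** Re-initiation concerns interrupted subjects, not permanently withdrawn ones. The sentence on final decisions can be read as assigning responsibility. They fail to resolve the conflict but do not clearly permit an override.

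A further objection is that permanent withdrawal may be too strict for an isolated Grade 3 laboratory or vital-sign value judged possibly related. That is a defensible view, but adopting it would mean changing the list and the synopsis. It is no reason to leave both rules standing.

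**Conclusion.** The contradiction on treatment-related Grade 3 toxicity is real and follows from the wording alone; it rests on no assumption. Grade 4 needs a clarification only.

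The consequence for an affected subject is up to three further vaccinations given against a stated contraindication. How many subjects this would touch is unknown and probably small; the chances in the working depend entirely on the assumed rates. A reader might infer that the analysis is compromised. It is not: Safety Analysis Set membership needs only one injection, and the planned analysis is descriptive.

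This should be fixed, for subject protection. The safeguards and the likely small number of cases keep it below the most serious grade.

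**What to change.** Amend Section 8.6 in three places.

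1. **Grade 3.** Events at least possibly related (Possible, Probable or Definite in Table 9) lead to permanent withdrawal from treatment, with study follow-up continued. Evaluation followed by continued dosing applies only to events judged Unrelated or Unlikely.
2. **Grade 4.** Keep immediate interruption for any Grade 4 event. Add that dosing stops permanently if the event is at least possibly related; otherwise withdrawal is discussed with the Medical Monitor.
3. **Discretion and re-initiation.** State that neither overrides the permanent-withdrawal list.

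The synopsis already carries the rule and needs no change. The cost is a protocol amendment submitted to the ethics committee, with approval awaited before use (Section 12.1.5). An administrative memorandum is not enough, because the change affects conduct and subject safety. No extra data are needed. The downside is that a few subjects may receive fewer doses, including for isolated Grade 3 laboratory or vital-sign values judged possibly related.
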